### Program assessment/evaluation

The assessment of the study outcome will be performed using a quantitative and a qualitative approach. Quantitative assessment will be conducted using questionnaires administered by the designated trainers, and the data will be fed into the Qualtrics software for data management. Before the training commences, all participants will take the pre-intervention test that measures their initial knowledge of oral health. The questions will be co-developed by Dental Public Health (DPH) consultants and educators on the research team based on available evidence and will be assessed for face and content validity before deployment. The questionnaire will also be pre-tested among participants who would not be involved in the study. The control group will be immediately provided with the post-intervention evaluation after the one-day lecture. After the training, participants in the training group will be assessed using the post-test. The pre and post-test scores will be compared for participants in the treatment and control groups. Participant’s capability to screen and detect oral diseases will be assessed post-intervention using picture tests.

After 3 months, a follow-up evaluation will be conducted. The number of logged referrals from the PHCs to the dental centers for oral health conditions will also be assessed for 3 months post-training based on the information logged by these providers (see Logic Model-Table 1). In addition, 5% of patients who were referred to dental centers as entered in the logbooks will be contacted via phone calls to verify their final visit to the dental centers.

The qualitative assessment to assess the impact of the training, points of improvement and the practicability of incorporation of oral health promotion activities into maternal and child health visits will be conducted with select participants in the intervention group at the 3-month evaluation using Deliberative Focus group discussions. This approach to evaluation serves to enhance program feedback through participants’ experiences and opinions. Refresher training will be conducted accordingly in month three if necessary. Data collection will be from February to May 2024.

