### Intervention and control

The intervention and control groups will consist of participants selected by a non-random process but with comparable characteristics. Across the three study sites, a total of 60 PHC workers (20 Nurses and CHWs at each site) will be assigned to the intervention group, and a corresponding number of participants will constitute the control group. Participants in the control group will receive a one-off conventional oral health education session consisting of a lecture on oral health, tooth brushing, and diet and oral hygiene demonstration using dental models. The intervention group will be exposed to the week-long pilot training on oral health education delivered by designated trainers (see Table 2). They will also participate in group activities such as oral exams and activity sheets. Each module is expected to last for approximately 4 h. Participants in the intervention group (those who will be trained) will be compared to the control group at each study site. Before the training begins, each participant will be administered a pre-intervention questionnaire to evaluate their oral health knowledge at baseline. The assessment will be repeated immediately after training and after 3 months. These evaluations not only serve as a means of monitoring training impact but also allow participants to observe how they improve throughout the training.

**Table 2 tab2:** Program and module delivery for the five-day training.

Day	Module
Day 1	Pre-intervention test Introduction to oral health
Day 2	Introduction to oral diseases and conditions
Day 3	Techniques in oral health promotion and oral disease prevention
Day 4	School and community-based oral health promotion
Day 5	MCOH Post-intervention test Facilitator assessment of participants capability to provide oral health education.

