## Discussion

Pilot studies are essential for improving the quality and efficiency of the major study (49). Thus, the success of this pilot program could help set the foundation for sustained oral health education training for primary health care workers, invariably creating a pool of qualified peer trainers for PHC workers, PHC patients, their families, and the general population. Studies have shown how misinformation, myths and cultural beliefs among individuals and community stakeholders negatively impact oral health attitudes and care-seeking behaviors in developing countries (50–54). Promoting approaches where qualified care professionals provide adequate and accurate oral health information may thus influence positive oral health practices, leading to improved oral health and overall health. The scope of the current project will encompass most of the essential components of primary oral care recommended by the WHO by leveraging the strategic positioning of the PHC system and its link with individuals, communities, and the health care system. These recommendations include “*age-friendly primary health care for oral health, maternal and child oral health care, health communication/oral health education, disease prevention methods, early detection, pain control - emergency care for oral health, continuity of oral healthcare, supportive referral systems and priority to those people most in need*” (7). The strength of the QED approach lies in its simplicity regarding data collection, ease of implementation and associated low cost (55). However, there are some limitations to this study design. Due to non-randomization of study participants, other factors related to the outcome of interest beyond the control of the researchers could potentially influence study results (56). Secondly, it is impossible to determine causality because quasi-experimental research is not an actual experiment; thus, only associations between interventions and outcomes can be made (43). Furthermore, because the treatment and control groups are nonequivalent (group assignment is by non-random selection), selection bias may exist. The presence of a nonequivalent no-treatment control in this study reduces issues such as threats to internal validity (i.e., observing the same participants over time). This is due to the assumption that the presence of similarity between the treatment and the control groups at baseline reduces the likelihood of having significant confounder differences between both groups (55, 57, 58).

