
In this study, we will ensure that a consistent approach is taken to select participants within and across study sites, administer evaluation surveys and follow-up (59). Additionally, we will conduct a pre-intervention assessment (allowing for the baseline comparison of the treatment and control group), an immediate post-intervention assessment, and 3 months following the training to allow for consideration of learning or attitude decay (43). Before use, the pre and post-tests will be validated for accuracy in measuring the outcomes of interest in the study. Also, tests will be scored consistently by a non-biased grader blinded to the participants and not part of the team that designed or conducted the oral health training (43). Regarding the establishment of causality, given that the intervention- (oral health education) comes before the assessment of the outcome, associations identified in QEDs meet an essential causality requirement (60).

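### The picture test of screening capability is stated as post-intervention only, so a group difference on it cannot be separated from prior skill in these non-randomised groups

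*Protocol article*

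**What the plan says.** The protocol article, *Program assessment/evaluation*, states that participants' "capability to screen and detect oral diseases will be assessed post-intervention using picture tests". It does not say which groups take the picture test. For baseline, the same section says that "all participants will take the pre-intervention test that measures their initial knowledge of oral health", and the *Intervention and control* section likewise describes the pre-intervention questionnaire as a knowledge measure. The controlled comparison is stated for that test: "The pre and post-test scores will be compared for participants in the treatment and control groups".

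*Study design* describes a pre/post study with a non-equivalent control group. *Participant recruitment* draws intervention participants from locations nearer the training centre and controls from more distant districts. The Discussion concedes that "because the treatment and control groups are nonequivalent (group assignment is by non-random selection), selection bias may exist". It relies on baseline similarity to limit confounding and presents the pre-intervention assessment as the means of comparing the groups at baseline. It also promises that "tests will be scored consistently by a non-biased grader blinded to the participants and not part of the team that designed or conducted" the training.

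Table 2 lists a separate item on Day 5 of the intervention programme: "Facilitator assessment of participants capability to provide oral health education". No control counterpart is stated.

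**The concern.** With non-random assignment, a post-only comparison contains any training effect plus whatever difference existed beforehand. The knowledge test handles this by being given before and after in both groups. The picture test, as described, does not. Recognising disease in photographs is named separately from knowledge, so the knowledge pre-test is at best a proxy for its baseline.

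At stake is how a picture-test result can be read. If trained workers score higher, the report could not say whether the course taught them to detect disease or whether workers nearer the centre were already better at it. If they score no higher, a prior deficit could be hiding a benefit. If controls do not take the test at all, there is no comparison to make.

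**Working it through.** **Plan's own figure.** 3 sites × (20 intervention + 20 control) = 120, that is 60 per group. This matches *Sample size estimation*. The stated minimum of 10 per group per site gives 3 × 10 = 30 per group. The article gives no power, effect size or SD, so there is no power calculation to reproduce.

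**Inputs from the article.** n = 60 per group (30 at the minimum); significance threshold 0.05.

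**Assumptions, not in the article.** The test is two-sided; both groups take the picture test; training has no effect on the picture score; the groups differ beforehand by d SD; observations are independent, so clustering by health centre is ignored.

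**Formula.** For a post-only comparison in SD units, SE = √(2/n). With b the part of the prior gap still present at post-test,

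P(reject) = Φ(b/SE − 1.96) + Φ(−b/SE − 1.96).

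At n = 60, SE = √(2/60) = 0.183.

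**Case 1: the gap persists in full (b = d).**

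| d (SD) | 60 per group | 30 per group |
|---|---|---|
| 0 | 5.0% | 5.0% |
| 0.1 | 8.5% | 6.7% |
| 0.2 | 19.5% | 12.1% |
| 0.3 | 37.6% | 21.3% |
| 0.5 | 78.2% | 49.1% |

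For example, with d = 0.3 and n = 60: 0.3/0.183 = 1.64; Φ(1.64 − 1.96) is about 0.376 and the other tail is negligible.

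**Case 2: the gap shrinks by the pre/post correlation r (b = r × d), with d = 0.3 and n = 60.**

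- r = 0.5: b = 0.15, b/SE = 0.82, rate 13.0%.
- r = 0.7: b = 0.21, b/SE = 1.15, rate 21.0%.

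The two cases are different assumptions about how stable the prior gap is. Case 1 is the more severe. Nothing in the article favours either.

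**The Day 5 assessment, read beside the picture test.** The picture test concerns detecting disease, while the Day 5 item concerns giving oral health education. The Day 5 item appears only in the timetable of the trained group and is made by a facilitator, not the independent grader. The article says the course is a "pilot training on oral health education delivered by designated trainers", with "questionnaires administered by the designated trainers". It does not say outright that the Day 5 facilitator is one of those trainers, although that is the natural reading. No arithmetic applies, because without a comparator there is no contrast to compute.

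**The case against.** The case for leaving this alone has real content.

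- **The measure is outside the hypotheses.** These cover knowledge scores and referral practices, and the article announces no controlled conclusion from the picture test. This stands and limits the consequence to a secondary capability result.
- **The limitation is conceded.** The Discussion admits selection bias and says only associations can be drawn. That is fair, but the same Discussion offers the baseline assessment as mitigation, and the picture test has none.
- **Obvious prior skill is excluded.** People with earlier oral health training, nurses in dental and maxillofacial units, and nurses who assisted with cleft education and surgery are not eligible. This makes a large gap less likely. It does not show that the groups are equal in recognising disease.
- **An article condenses the full protocol.** Who takes the picture test may be set out there, so silence on that is not itself an error. The timing, however, is stated, and it is post-intervention.

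A reader might go further and infer that neither capability measure can support a controlled or blinded conclusion. The text does not support that. The blinded grader is promised for tests and may well score the pictures; the passage is about the pre- and post-tests, so this is unclear rather than excluded. Nor does the article say that controls skip the picture test. If they take it, the comparison is controlled but has no baseline. A reader might also treat the Day 5 item as a second rating of screening skill that contradicts the blinding promise. It measures something else, is not named as an outcome or group comparison, and may lean favourable without being bound to.

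**Conclusion.** The point holds for the missing baseline. As stated, the picture test is post-intervention only in groups formed by geography, so a between-group difference on it cannot be separated from a prior difference in skill. It does not touch the knowledge comparison, which has a baseline in both groups.

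The size is unknown because the article gives no imbalance. The illustrative range at 60 per group runs from 8.5% false positives for a 0.1 SD gap to about 38% for a 0.3 SD gap that persists in full; a 0.3 SD gap that partly regresses gives 13% to 21%. These figures depend on the assumed gap, its persistence, a two-sided test, both groups being tested, and no clustering.

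The Day 5 facilitator assessment is a minor reporting matter: it has no stated control counterpart and is not independently graded, so it cannot serve as evidence of a training effect.

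**What to change.** 1. State that both groups take the picture test. Include the same or a parallel picture set in the existing pre-intervention test and in the post-test of each group.
2. State that the blinded, independent grader scores it.
3. Compare groups with adjustment for the baseline picture score. If no baseline is collected, report the picture test as descriptive only.
4. Label the Day 5 facilitator assessment as course feedback, not as a comparative outcome.

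**Cost.** The pre-test session already exists for all participants, so this adds a few items and a few sentences. The added items, and any parallel set, need the validation the article already promises for its tests. Pre-test sensitisation is possible and may differ between groups: controls are post-tested straight after a one-day lecture and trained workers on Day 5, so the time to recall or look up the pictured conditions differs.

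**Limit of the fix.** Adjustment reduces the bias but may not remove all of it. If a 0.3 SD gap is fully stable while individual scores correlate at r, covariance adjustment leaves (1 − r) × 0.3, that is 0.15 SD at r = 0.5 and 0.09 SD at r = 0.7. Showing the baseline picture scores by group lets readers judge what remains.

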In step 3, we identified an evidence-based approach most likely to influence change using the Lay Health Worker Model/Promotora de Salud (32), a public health model of workforce development targeted at health professionals such as community health workers, in this context, who lack formal oral health training but are members of the communities that they work in (33, 34). This model is often utilized to improve and support access to care in settings with workforce shortages (35). Although this is not commonly used in this population, the promising outcomes reported as it concerns oral health-related knowledge and behaviors in minority populations (36–39) and the need for a more competent allied health workforce capable of providing culturally appropriate oral health care in Nigeria makes it applicable to this study. By exploring parallel processes through collaborative partnerships and considering cultural nuances in the curation of training materials to maximize relevance and acceptability, we anticipate an impactful and lasting program outcome. This led to the fourth step, where program components, like training modules, assessment questions, activity sheet and the logbook for evaluation, were designed following extensive deliberation with all stakeholders. For the fifth and sixth steps, we established how, when, and where the training will be implemented and developed an evaluation plan to assess the effectiveness of the program. In this case, the impact of OHE-NCHeW will be immediately evaluated post-intervention and after 3 months in the training and intervention group.

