#### Null hypothesis

No measurable difference will be observed in the post-intervention knowledge scores and referral practices as it relates to oral health between participants with access to the 5-day training workshop vs. the control group.

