### Study design

We will utilize a quasi-experimental design (QED) (pre-and post-with a nonequivalent control group) to assess the impact of a five-day pilot oral health education program on the knowledge level and referral practices of Nurses and Community Health Workers in PHCs in three States in Nigeria - (Lagos, Oyo and Kano). A three-month post-training evaluation will follow this. A pre-training evaluation will be conducted prior to the commencement of training, and a post-evaluation will be conducted immediately and 3 months after training. Furthermore, we have included a qualitative assessment via unstructured interviews with the program trainers to explore their experience delivering the training modules and interacting with participants. We will also conduct a focus group discussion (FGD) with the participants in the intervention group to have an in-depth understanding of their opinions, training impact and points of improvement at the 3-month post-training evaluation. Quasi-experiments are often conducted to assess the effectiveness of a treatment, such as educational intervention in field settings where random assignment is not feasible (40–42). This method remains a quick and convenient approach to evaluating a target group to which an intervention has been applied (43).

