### Participant recruitment

The permission to conduct the study was sought, and relevant approvals were obtained from the Permanent Secretary (PS) of the State Primary Boards, Permanent Secretaries of State Health Districts, Director of Nursing Services and the Director of Community Services. Nurses who are in the dental and maxillofacial unit and/or nurses who have assisted with Smile Train education and surgeries were excluded. The nominal rolls of nurses and community health workers in the State Health Districts served as the sampling frame, and five nurses and five community health workers who met the selection criteria were selected from each district by simple random sampling (balloting). To avoid contamination, participants from Health districts who were from more distant locations were selected for the control group, while the participants from locations closer to the training center were selected for the intervention group. Following the IRB approval from the Ethics Committee of the participating centers, each recruited participant signed a written consent before active recruitment into the study.

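### Referral practice has no pre-training measurement, so with groups set by distance a pre-existing near/far difference in referrals cannot be told apart from a training effect

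*Protocol article*

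**What the plan says.** The Study design section announces a quasi-experiment, "pre-and post-with a nonequivalent control group", and applies it to two outcomes together, in both cadres of worker: "to assess the impact of a five-day pilot oral health education program on the knowledge level and referral practices of Nurses". The null hypothesis also covers both outcomes: "No measurable difference will be observed in the post-intervention knowledge scores and referral practices as it relates to oral health". The Logic Model (Table 1) lists a rise in referrals to dental centres as a short-term outcome.

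The measurement is set out under Program assessment/evaluation: "The number of logged referrals from the PHCs to the dental centers for oral health conditions will also be assessed for 3 months post-training". The count is taken from records that the providers keep themselves. The section on program development with the intervention mapping framework says the logbook was designed as one of the programme's own components. The pre-intervention questionnaire is described twice, under Intervention and control and under Program assessment/evaluation, and both times as a measure of oral health knowledge.

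On how the groups were formed, Participant recruitment states that "participants from Health districts who were from more distant locations were selected for the control group", and that those nearer the training centre went to the intervention group.

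On who is followed, the intervention mapping section says the impact will be "immediately evaluated post-intervention and after 3 months in the training and intervention group". Intervention and control has every participant assessed before, immediately after and 3 months after training.

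**The concern.** A pre/post controlled design protects against unequal groups by comparing each group with its own starting level. For knowledge that starting level exists. For referrals, as described, it does not, so the design reduces to a single post-training comparison of two groups chosen to differ in location.

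The Discussion answers the selection problem by relying on the groups being alike at baseline and on a baseline comparison. Neither can be checked or used for referrals. Because nearness and training coincide by design, adjusting for distance afterwards has little or no overlap to work with.

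What is at stake is the interpretation of one of two headline outcomes. The Sample size estimation section says the pilot data will be used to size the major study, so a confounded referral contrast could carry forward into it.

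**Working it through.** **1. The plan's own figure.** 3 sites × 20 per group × 2 groups = 120, or 60 per group. This reproduces the stated total. No power calculation, referral rate or effect size is given.

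**2. What each outcome has.**

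| | Knowledge | Referrals |
|---|---|---|
| In the design statement and hypotheses | yes | yes |
| Pre-training measurement described | yes | none |
| Post-training measurement | immediate and 3 months | logged over 3 months |
| Control group explicitly measured | yes | not stated |

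**3. Size of the problem for a post-only comparison.** All rates here are assumed. The inputs are a mean of 5 logged referrals per nearby worker in 3 months; negative binomial counts with k=1, so variance = μ + μ²; 60 independent workers per group; no training effect; two-sided 5% test.

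Formula: z = (difference in means) / √((variance near + variance far)/60). The chance of p<0.05 is Φ(z − 1.96) + Φ(−z − 1.96).

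- Control rate 0.7 of the nearby rate: means 5 and 3.5; variances 30 and 15.75. SE = √(45.75/60) = 0.873; z = 1.5/0.873 = 1.72; chance about 0.40.
- Control rate 0.8: means 5 and 4; variances 30 and 20. SE = √(50/60) = 0.913; z = 1/0.913 = 1.10; chance about 0.195.

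**4. Sensitivity to the assumptions.** A simulation used control means of 2, 5 and 10, less overdispersion (gamma shape 2), no district variation and no training effect, with 1,500 runs per scenario. The share of runs with p<0.05, across the three means, was:

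| Near/far ratio | Post-only t-test | Post-only rank test | Change from baseline |
|---|---|---|---|
| 1.0 | 4–6% | 5% | 4–6% |
| 1.25 | 25–35% | 20–30% | 5–6% |
| 1.5 | 63–82% | 54–76% | 5–6% |

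A ratio of 1.25 is the same as a control rate of 1/1.25 = 0.8. The higher percentage here than in step 3 reflects the smaller overdispersion. The rank test is nearly as exposed as the t-test, because the groups really do differ; the difference is simply not due to training.

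**5. What the last column depends on.** The simulated change comparison (on the log scale) stays near 5% because the near/far ratio is the same before and after training and both counts are obtained in the same way in the two groups. A baseline removes a stable difference. It does not remove different trends or different logging habits.

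**6. Timing.** Data collection runs from February to May 2024, about 4 months. A prospective 3-month baseline plus 3 months of follow-up needs 6 months and does not fit. A retrospective count does.

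**The case against.** Several points on the other side have weight.

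- **The hypothesis can be answered as worded.** A reader might infer that half the hypothesis is unanswerable. The hypotheses concern a post-intervention difference between groups, and if both groups keep logs, that difference can be estimated. What is lost is the ability to attribute it to training.
- **The limitation is partly admitted.** The Discussion concedes possible selection bias and limits conclusions to associations. It would therefore be too strong to say that a near/far difference will be read as a training effect. The admission is general, though, and the remedy the Discussion offers, a baseline comparison, is missing for this outcome.
- **Distance is measured to the training centre, not to dental centres.** That it tracks referral habits is plausible, but the documents neither show nor quantify it.
- **The questionnaire is not shown.** The Discussion says the tests will be validated for the outcomes of interest, and the research question includes referral practices, so a self-reported referral item cannot be excluded. It would still not be a baseline for the logged count, and both descriptions of the instrument mention knowledge.
- **The analysis section allows nonparametric tests.** A complaint that t-tests suit skewed counts poorly is therefore not supported. The confounding remains under either test.
- **The phone check has another purpose.** "5% of patients who were referred to dental centers as entered in the logbooks will be contacted via phone calls" to confirm that they attended. It is not presented as validation of the logs, so its size is no fault here; equally, it supplies no baseline.
- **The intervention mapping sentence may be a slip.** It names one group twice, and Intervention and control assesses everyone at 3 months. Even so, no section says that controls keep logbooks.

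**Conclusion.** The point holds in this form: the protocol claims a pre/post controlled design for referral practice but describes only a post-training, provider-logged count, in groups separated by distance. A pre-existing near/far difference in referrals cannot be told apart from a training effect.

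Under the assumptions in step 3, a modest existing difference (control rate 0.7 to 0.8 of the nearby rate) would alone give a significant post-only t-test about 20% to 40% of the time, against the nominal 5%. The qualitative conclusion needs no particular rate; the percentages depend entirely on assumed rates and ignore clustering. The documents do not establish that such a difference exists.

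Whether controls keep logbooks also needs to be stated. If they do not, even the post-training comparison between groups is missing.

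**What to change.** 1. Add to both groups' pre-intervention questionnaire the number of dental referrals made in the previous 3 months. Take the same count from facility registers if they exist; the documents do not mention any.
2. Issue the same logbook to both groups from the same date, say so under Program assessment/evaluation, and correct the intervention mapping section so that the 3-month evaluation covers the intervention and control groups.
3. Compare the change in referrals from baseline between groups, instead of the post-training count alone.
4. If no baseline can be obtained, report referrals as descriptive and remove them from the hypotheses.

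The cost is one or two questions, logbooks for 60 controls if they do not already have them, and a change of analysis wording. Recalled counts are noisy and come from a different source than the logs, so register counts are preferable where available. Keeping a log may slightly raise referrals among controls, which would shrink the contrast rather than inflate it.

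### The protocol allows refresher training in month three without placing it after the 3-month questionnaire and the close of the 3-month referral log

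*Protocol article*

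**What the plan says.** All of this comes from the protocol article; no analysis plan is at hand.

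- **Refresher** (Program assessment/evaluation): "Refresher training will be conducted accordingly in month three if necessary". Neither the recipients nor the criterion for need is given.
- **Knowledge test** (Intervention and control): "The assessment will be repeated immediately after training and after 3 months". Program assessment/evaluation agrees: "After 3 months, a follow-up evaluation will be conducted".
- **Purpose of the late test** (Discussion): it is held "3 months following the training to allow for consideration of learning or attitude decay".
- **Referrals** (Program assessment/evaluation): the logged number "will also be assessed for 3 months post-training based on the information logged by these providers".
- **Focus groups** (same section, shortly before the refresher sentence): held with selected participants "in the intervention group at the 3-month evaluation using Deliberative Focus group discussions".
- **Controls** (Intervention and control): "Participants in the control group will receive a one-off conventional oral health education session". No refresher is described for them.

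The null and alternate hypotheses name two outcomes, post-intervention knowledge scores and referral practices. Both have a 3-month component.

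**The concern.** The 3-month questionnaire is informative about retention only if nothing re-teaches the material between the immediate post-test and that questionnaire. The 3-month referral count reflects the five-day training only if no further training falls inside the window. The refresher sentence names a time that, taken at face value, overlaps the referral window and comes before a test held once three months have passed.

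Two features would make an early refresher awkward to interpret. It depends on perceived need, so if need reflects weak retention, the sites that had lost most would be the ones re-trained, and decay would be hidden where it was largest. It also appears to be meant for the trained group, so it would not cancel out in the comparison with controls. The section Sample size estimation says the pilot data will be used to size the main study, so an inflated 3-month difference could carry forward.

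**Working it through.** The protocol attaches no figure to this point, so there is none to reproduce. The check is one of sequence, followed by illustrations whose effect sizes are assumed.

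**Sequence, counting months from training**

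| Reading | 3-month knowledge test | 3-month referral count |
|---|---|---|
| A. Refresher during the third month, evaluation after that month ends | refresher comes first; retention measure affected | window still open; affected |
| B. Evaluation held within the third month, refresher later in that month | unaffected | window still open; affected |
| C. Month three used loosely for the 3-month visit, refresher after all measurement | unaffected | unaffected |

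Only reading C is clean, and the protocol does not state it. Data collection from February to May 2024 does not settle the matter. If calendar months of that period were meant, the third would be April, before collection ends.

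**Referral count**

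Month three is 1/3 of a 3-month window. Assume a constant referral rate that the refresher multiplies by r for the remaining fraction f of the window. The relative increase in the trained group's total is f × (r − 1).

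| Assumed r | Start of month three (f = 1/3) | Middle of month three (f = 1/6) | After the window closes (f = 0) |
|---|---|---|---|
| 1.2 | 0.2/3 = 6.7% | 0.2/6 = 3.3% | 0 |
| 1.5 | 0.5/3 = 16.7% | 0.5/6 = 8.3% | 0 |
| 2.0 | 1.0/3 = 33.3% | 1.0/6 = 16.7% | 0 |

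The first column is the upper end for each r, since a refresher in month three cannot affect more than one third of the window.

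**Knowledge score (reading A only)**

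Assume an immediate advantage of 0.8 SD and a true 3-month advantage of 0.5 SD without a refresher. The true loss is 0.3 SD, or (0.8 − 0.5)/0.8 = 37.5%, about 38%. Let the refresher restore a share k of that loss before the test.

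- k = 0: observed advantage 0.50 SD, apparent loss 38%, no bias.
- k = 0.5: observed 0.5 + 0.5 × 0.3 = 0.65 SD, apparent loss 0.15/0.8 = 19%, retention overstated by 0.15 SD.
- k = 1: observed 0.80 SD, apparent loss 0%, retention overstated by 0.3 SD.

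Under readings B and C this bias is zero.

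**The case against.** The best case against is that the refresher is meant to follow the evaluation. The sentence comes after the description of focus groups at the 3-month evaluation, which ask about points of improvement, and the word *accordingly* points back to that feedback. The trigger fits too. The protocol describes no assessment between the immediate post-test and three months, so there would be no planned data to show need any earlier. The article also uses several phrases for the same 3-month timepoint, and *in month three* may be one more. Finally, this is a condensed article of a pilot whose authors claim associations only, and detailed scheduling may sit in the full protocol.

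Most of this stands. A reader might infer that the plan schedules re-training before the 3-month test. The documents do not support that: no passage states that order, and the context makes the later order at least as plausible. A reader might also take it as stated that only the trained group is re-trained. That is a reasonable inference, because controls receive a single session and a refresher presupposes training, but the recipients are not named.

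The objection does not remove the overlap. Even if the refresher follows the evaluation, one given within the third month falls while referrals are still being counted (reading B). The context also links the refresher to the focus groups, and nothing says that the questionnaire and the logbook must be closed first. The point concerns a timing that the article does state, against two measurement periods that it also states, so condensation is not a full answer.

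**Conclusion.** The point holds as an unsecured sequence. The protocol permits a need-triggered refresher in month three and does not place it after the 3-month questionnaire and the end of referral logging. On the literal reading it can affect up to one third of the referral window and can precede the retention test. If it follows the 3-month evaluation, the knowledge test is unaffected; if it follows all measurement, both outcomes are.

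The size cannot be determined from the documents. The 6.7% to 33.3% range for referrals assumes a constant baseline rate, a refresher at the start of month three and a rate multiplier between 1.2 and 2.0. The 0.3 SD and 38% for knowledge rest wholly on assumed advantages of 0.8 and 0.5 SD and full restoration. These figures show what is at risk and are not estimates of bias in this study.

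**What to change.** Replace the refresher sentence with one that fixes the order, for example: *Any refresher training will be offered only after the 3-month questionnaire, the close of the 3-month referral log and the focus group at that site are complete.* State also which group is to receive it.

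If any refresher was given earlier, report its dates and recipients by site. Add a sensitivity analysis that counts referrals only up to the refresher date, cutting off the controls at that site after the same length of follow-up. Describe any 3-month score obtained after a refresher as such, not as retention.

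The change costs one sentence, and any refresher moves later by days to weeks. The sensitivity analysis needs dated logbook entries and shortens follow-up at the affected sites, so it loses some referrals.
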